**3.3** **Evidence for SoroTouch**

SoroTouch is an iPad application with a unique interface, called 'invisible mode' (where the beads are not displayed), which requires the learner to visualize and manipulate the beads in his/her mind in order to solve the problems. Furthermore, SoroTouch trains fast and accurate manipulation of the beads and has features that facilitate continuous learning. Analysis of learner data showed that 54% of leavers in 2017 and 62% in 2018 had successfully mastered their mental arithmetic skills by the time they left the program. The time spent using SoroTouch for skill acquisition has been validated to fall between 7 and 26 months.^6)^

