**5.7** **How to manage medicines and other products**

Management of the application

This application is to be carried out by the research participants themselves using the iPads loaned by Digika Ltd. The company and the research participant sign a contract based on separate monitoring terms and conditions, and the research participant is responsible for managing the iPad themselves during their participation in the research.

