**9.2** **Methods and timing of evaluation, recording and analysis of safety measures**

Investigators will document in the medical record the time of onset and outcome of the disease or defect, severity, outcome, causal relationship to the study and the course of the disease or defect. The severity will be judged according to the following criteria, and the severity will be judged as 'serious' or 'non-serious' based on the criteria in section '9.4 Procedures for collecting, recording and reporting information on diseases and other conditions'.

[Criteria for determining severity]

1) Mild: No treatment is required and the patient recovers.

2) Moderate: Cases in which treatment is required to continue wearing the test device. Cases requiring additional treatment/procedure for post-operative diseases or defects.

3) Severe: Cases in which the continuation of the wearing of the test device is difficult.

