**9.3** **Method and timing of analysis on safety measures**

Detailed in section '10. Statistical analyses.

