**13.1.2　Expected disadvantages and burdens and measures to minimise them**

Participants in the intervention group may experience psychological strain from performing the SoroTouch for up to 30 minutes a day.

Participants in the control group may also experience time constraints and physical strain from cooperating with the examinations.

The staff of the Consortium for Dementia Prevention and Action will provide support such as talking and encouragement to reduce this burden.

1. **Management and storage of records (including data) and samples**

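### Two of the three severity grades in section 9.2 rest on a worn device and surgery that this app trial does not have, and section 9.3 points to a safety analysis that section 10 does not contain

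*Protocol*

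**What the plan says.** Protocol section 9.2 asks investigators to document onset, outcome, severity, causal relation and course for each disease or defect, and gives three severity grades:

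- Mild: "Mild: No treatment is required and the patient recovers".
- Moderate, first sentence: "Cases in which treatment is required to continue wearing the test device".
- Moderate, second sentence: "Cases requiring additional treatment/procedure for post-operative diseases or defects".
- Severe: "Cases in which the continuation of the wearing of the test device is difficult".

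The same section sends the serious/non-serious decision to the criteria in section 9.4.

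On the method and timing of the safety analysis, section 9.3 says only: "Detailed in section '10. Statistical analyses".

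The intervention is described elsewhere. Section 3.3 states that "SoroTouch is an iPad application with a unique interface", and section 5.7 that "This application is to be carried out by the research participants themselves using the iPads loaned by Digika Ltd". Section 5.2.1 calls the study non-invasive. Section 5.3 allocates participants 1:1 to the app or to a non-treatment group, and the flow in section 5.2.2 plans 10 in each.

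**The concern.** The Moderate and Severe definitions appear to belong to a different kind of study, one with a worn device and an operation. An investigator who has to grade an event here has no literal basis for choosing either. The control arm is worse placed, because controls have no study product of any kind whose continued use could become difficult.

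What is at stake is whether severity can be graded consistently and compared between arms. Each investigator would have to improvise, and might do so differently for app users and for controls. With 10 planned per arm and no blinding described, a few inconsistently graded events could shape how the severity profile looks.

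The second issue is a reference with nothing behind it. A reader who follows section 9.3 to learn how and when safety will be analysed finds no answer.

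**Working it through.** No arithmetic beyond a count applies. The check sets the definitions against the trial's own description, then section 9.3 against section 10.

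**Step 1. What each grade depends on, and whether it can be met.** Two readings are tried: the literal one, and a generous one in which wearing is a loose translation of using.

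| Grade (9.2) | Depends on | App arm (n = 10), literal | App arm, wearing = using | Non-treatment arm (n = 10), either reading |
|---|---|---|---|---|
| Mild | no treatment, and recovery | usable | usable | usable |
| Moderate, first sentence | treatment in order to go on wearing the device | not usable | usable | not usable |
| Moderate, second sentence | treatment after an operation | no referent | no referent | no referent |
| Severe | difficulty in going on wearing the device | not usable | usable | not usable |

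The second Moderate sentence could apply only by accident, if a participant happened to have unrelated surgery. No operation is part of this trial.

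**Step 2. Count.**

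- Literal reading: 2 of 3 grades are unusable in both arms, so 10 + 10 = 20 planned participants have no grade above Mild.
- Generous reading: the two device-based criteria work in the app arm but not in the control arm, so 10 of 20 planned participants (half) have no grade above Mild.

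**Step 3. Which events fall through.** An event that needs treatment is not Mild, because Mild requires that none is needed. On the literal reading it meets neither higher grade, in either arm. On the generous reading the same event can be graded in an app user and not in a control. An event that needs no treatment but does not resolve also fails Mild, which requires recovery.

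**Step 4. Section 9.3 against section 10.**

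| Section | Content |
|---|---|
| 10.1 | subjects for the efficacy analysis |
| 10.2 | target number and rationale |
| 10.3, 10.4 | review of subjects, data handling, missing values |
| 10.5.1 | background factors in the efficacy population |
| 10.5.2 | CogEvo change by analysis of covariance |
| 10.5.3 | MoCA-J and SF36 by unpaired t-test |
| 10.6 | time points for those outcomes, possible subgroups |

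None of these sets out a population, summary or timing for adverse events. The reference in section 9.3 therefore has no target.

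**Step 5. What does not depend on the grades.** Seriousness and the 7-day and 15-day reporting deadlines are set by section 9.4. Discontinuation after an adverse event (section 6.4, item 5) turns on the investigator's decision, not on a grade. No analysis or stopping rule in the protocol uses Mild, Moderate or Severe.

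**The case against.** The best case on the other side has four parts.

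**It is a translation problem.** The English is rough in places, and wearing may simply stand for using. The post-operative sentence is an additional case under Moderate, so its irrelevance does not disable the sentence before it. This stands for the app arm. A reader might infer from the wording that no participant could ever be graded above Mild; that holds only on the literal reading. The defence does not reach the control arm, which has nothing to use, and it does not explain the mention of surgery.

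**Little depends on the grades.** This stands. A reader might infer that serious events could go unreported. The documents do not support that, because section 9.4 works independently of the severity grades. Nor do they show that ungradable events would be common. The harm foreseen in section 13.1.2 is that app users "may experience psychological strain from performing the SoroTouch for up to 30 minutes a day", and the planned response is staff support and encouragement, so such an event would ordinarily be Mild if the person recovers.

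**A safety population and tabulation belong in a separate statistical analysis plan.** Partly right: section 25 mentions a statistical analysis plan among the documents to be submitted, and one may exist. But section 9.3 does not defer to it. It says the detail is in section 10 of this protocol, and the opening of section 10 speaks of a plan established within the protocol. The point is the false reference, not the absence of detail.

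**Safety would not be confined to the efficacy set.** A reader might infer that participants left out of the set in section 10.1.1 would also drop out of the safety count. Nothing says so. That set is labelled for efficacy, and section 9.1 covers events identified during the participation period with no exclusion.

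**Conclusion.** The point holds as an internal inconsistency with modest consequences. Section 9.2 requires a severity grade but defines two of its three grades by circumstances that the trial does not have. On the literal reading, an event needing treatment cannot be graded in either arm. On the most favourable reading, which assumes that wearing means using, the gap remains for the 10 planned controls. Either way, severity cannot be graded consistently or compared between arms. Section 9.3 also refers to a safety analysis that section 10 does not contain.

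The serious/non-serious classification, expedited reporting and the efficacy analysis are not affected. The conclusion rests on the protocol text alone. It assumes nothing about how many events will occur or how severe they will be.

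**What to change.** 1. **Section 9.2.** Reconcile the severity definitions with the intervention actually studied, in terms that apply in both arms and make no reference to wearing or surgery. Between them the grades should cover every event, including one that needs no treatment but does not resolve. The content of each grade is for the investigators to decide. The separation from the seriousness decision in section 9.4 is already in place and should stay.
2. **Sections 9.3 and 10.** Make the reference true or correct it. One way is a short item in section 10 stating that events will be tabulated by arm in all randomised participants. The period should be the one the protocol already sets: section 9.1 points to section 5.5, which runs to 30 September 2022, and section 9.5 continues follow-up of an event until it disappears or follow-up is judged unnecessary. A new window ending at month 6 would conflict with those sections.

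The cost is a minor protocol revision. Section 22.2 requires approval by the accredited review committee and a stated effective date. Sections 9.1 and 9.2 already provide for the events and their details to be recorded, so no further data collection is needed.

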**9.3** **Method and timing of analysis on safety measures**

Detailed in section '10. Statistical analyses.

**9.4** **Procedures for collecting, recording and reporting information on diseases and other conditions**

When co-investigators obtain information on the following matters, they report it to the administrator of the implementing medical institution and the principal investigator within the respective timelines stipulated. The principal investigator reports the matter to the accredited clinical research review committee and promptly informs the other research assistants. Then, the other co-investigators will promptly report the matter to the administrator of the implementing medical institution. In addition, when the principal investigator obtains information on the matters in ① and ② (a), he will also report it to the Minister of Health, Labor and Welfare within the stipulated period of time.

①Predictable matters are those described in the study device summary, the study protocol or the consent document. The following diseases etc., the occurrence of which is suspected to be due to this study and which cannot be predicted.

[Reporting period] 7 days.

(a) Death.

(b) Diseases, etc. that may lead to death.

② The following matters in cases where this research is conducted.

[Reporting deadline] 15 days

(a) The following diseases, etc., which are suspected to be caused by this research (excluding those falling under 9.4 ①)

(1) Death

(2) Diseases, etc. that may lead to death

(b) The following diseases, etc., which are suspected to be caused by this research and cannot be predicted (excluding those listed in 9.4 ①)

(1) Diseases requiring hospitalisation or prolonged hospitalisation for treatment, etc.

(2) Disability

(3) Diseases, etc. that may lead to disability

(4) Illnesses, etc. that are serious enough to be related to illnesses (1) to (3) and death or illnesses that are likely to lead to death

(5) Congenital diseases or abnormalities in later generations

③ Diseases suspected to be caused by this research (excluding those listed in ① and ②).

[Reporting deadline] When periodic reports are made to the Authorized Clinical Research Review Committee.

When making reports on ① to ③ above, information should be provided to the company manufacturing the device at the same time.

**9.5** **The observation period for participants in the study after the incidence of disease, etc.**

Research subjects after an outbreak of disease, etc., are followed up until the disease, etc., disappears or until the principal investigator (co-)investigator decides that it is no longer necessary.

1. **Statistical analysis**

If the statistical analysis plan is changed from that established within the protocol, the research protocol should be revised.

**10.1** **Subject of analysis**

10.1.1　 Subjects for efficacy analysis

All randomized subjects, excluding those with no intervention at all and those with no post-intervention assessments at all.

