5.2.2 Clinical research flow/outline

Registration to allocation should be done within 4 weeks. (Assessment allocation period).

Intervention group（n = 10）

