**Intervention period （6 months）**

Control group（n = 10）

Enrolment

Informed consent

Random allocation

The principal investigator explains and obtains consent from the study subjects via online tools such as Zoom in order to prevent the spread of COVID-19 infection. The consent forms are converted into PDF format by the staff of the Consortium for Dementia Prevention Activities, and shared on a password-protected Dropbox and sent to the principal investigator. The paper consent forms are then promptly destroyed.

Schedule of the trials

| Evaluation item | **Registration to allocation should be done within 4 weeks. (Assessment allocation period)** | **One month after** | **Two months after** | **Three months after** | **Four months after** | **Five months after** | **Six months after** |
| --- | --- | --- | --- | --- | --- | --- | --- |
| Obtaining consents | ● |  |  |  |  |  |  |
| Investigation of Characteristics | ● |  |  |  |  |  |  |
| **MoCA-J** | ● |  |  |  |  |  | ● |
| SF36 | ● |  |  |  |  |  | ● |
| CogEvo^®︎^ | ● | ● | ● | ● | ● | ● | ● |
| Investigation of adverse events |  | | | | | | |

The participants will conduct the following curriculum in order from J1, as described in the user manual (Ref. 1). The participants will try to complete each stage, which has 30 missions, three aspects in 30 minutes each day.

The learning time is displayed on the SoroTouch recording screen and the learning time and mission completion status are checked by the staff of the Consortium for Dementia Prevention Activities.

If there are participants whose average daily learning time is less than 10 minutes, the data will be analyzed only for the periods when they were able to do more than 10 minutes.

Ref.1 SoroTouch curriculum

**
[figure not shown]
**

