**5.3** **Methods of case registration and allocation**

The principal investigator (co-investigator) explains the subject of the study in accordance with the explanatory document and, if consent is obtained, registers and allocates the subject as a research participant. Research participants will be given an identification code for anonymization purposes, which will be used as the identification code for research participants in this study.

The study will be conducted in a randomized comparison to ensure that the allocation does not result in differences in medical background between treatment groups. The participants will be allocated in a 1:1 ratio to the SoroTouch treatment group and the non-treatment group using Muzinwali (https://mujinwari.biz/users/login). The allocation method will be stratified block allocation with CogEvo®︎ (index below and above 70) as allocation factor. After obtaining consent from the study participants, investigators will access Muzinwali to confirm the allocation of the intervention to the study participants concerned. As soon as possible after confirming the allocation, the 'Allocation Instructions/Confirmation Form' is signed and dated. After obtaining consent from the research subject to participate in the research and conducting the allocation, the investigator in charge of the research should ensure that all 'allocation instructions/confirmation forms' are properly kept by the principal investigator.

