**8.2　 Evaluation of Efficacy**

8.2.1.　Primary outcome

The intervention is deemed effective if there is a statistically significant difference in changes of CogEvo®︎ scores between the intervention and control groups.

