**10.2** **A target number of subjects and rationale for setting the number**

The target number of subjects: 20

［Rationale] Based on the results of the present study on cognitive function and quality of life, a larger-scale validation study is planned in the future. Therefore, this study is an exploratory study, and the number of patients was set at 20 which is the maximum number of patients that can be conducted at the relevant institution. If the intervention in this study has an effect size of 1.4 on the CogEvo change, the probability of error for Type 1 and Type 2 can be assessed as 0.05 and 0.2 respectively with 20 analysis subjects.

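### The efficacy set's no-intervention exclusion is undefined for untreated controls and can remove only SoroTouch participants who never start

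*Protocol*

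**What the plan says.** Section 10.1.1 gives the only efficacy population in the protocol: "All randomized subjects, excluding those with no intervention at all and those with no post-intervention assessments at all".

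Section 5.3 describes the arms. Participants are "allocated in a 1:1 ratio to the SoroTouch treatment group and the non-treatment group". The flow outline in 5.2.2 plans 10 per arm, and no sham, placebo app or control activity is described. Section 8.2.1 judges success by a "statistically significant difference in changes of CogEvo®︎ scores between the intervention and control groups", so 'intervention' in this protocol means SoroTouch as opposed to control.

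Section 10.2 sizes the trial on a standardised effect of 1.4 and says that "the probability of error for Type 1 and Type 2 can be assessed as 0.05 and 0.2 respectively with 20 analysis subjects". The number to be recruited is also 20, so there is no allowance for loss.

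Section 6.4 bears on the same people. Its item 8 lists not carrying out the task as instructed as a ground for discontinuing a participant, and the section ends observation at discontinuation.

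**The concern.** An analysis set should be defined by criteria that can be met in either arm and that do not depend on what happens after allocation. The no-intervention exclusion fails on both counts. A control has nothing to start, so the criterion either has no meaning for that arm or would be met by every member of it. For the SoroTouch arm it turns on behaviour after allocation. Participants know whether they were given an app to use for 30 minutes a day, so failing to start can depend on the allocation. Participants with equally little motivation who were allocated to control stay in.

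If never-starters would also have done less well on CogEvo, removing them raises the SoroTouch mean with no matching change in the control mean. With 10 per arm, each such exclusion is 10% of the arm. The phrase 'post-intervention' in the second exclusion is also undefined for controls, although that criterion can at least remove people from either arm.

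**Working it through.** **Inputs from the protocol.** 10 per arm (5.2.2); effect size 1.4, type 1 error 0.05, type 2 error 0.2, 20 analysed (10.2). Sidedness is not stated; two-sided is assumed.

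**Inputs assumed.** The number k of SoroTouch never-starters, and the correlation r between engagement and CogEvo change. The protocol gives neither.

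**Step 1: reproduce the stated sample size.** For a two-sample t-test, power is taken from the noncentral t distribution with n1 + n2 − 2 degrees of freedom and noncentrality 1.4 × √(n1·n2/(n1 + n2)).
- 9 vs 9: noncentrality 1.4 × √4.5 = 2.970, power 0.796.
- 10 vs 10: noncentrality 1.4 × √5 = 3.130, power 0.841.

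The smallest equal allocation with at least 80% power is 10 per arm, so the stated 20 reproduces. Giving up one degree of freedom for a covariate changes 0.841 only to 0.839.

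**Step 2: apply the exclusion to the SoroTouch arm only, keeping all 10 controls.**

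| k removed | Analysed (SoroTouch vs control) | Power at 1.4 |
| --- | --- | --- |
| 0 | 10 vs 10 | 0.841 |
| 1 | 9 vs 10 | 0.819 |
| 2 | 8 vs 10 | 0.791 |
| 3 | 7 vs 10 | 0.757 |

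One exclusion leaves power above the stated 0.80. Two take it just below.

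**Step 3: shift in the SoroTouch mean when there is no true effect.** Suppose the k never-starters are the least engaged of 10, with engagement standard normal. The two lowest of 10 standard normal values have expectations −1.539 and −1.001. Dropping the lowest k raises the mean engagement of those who remain by the sum of the dropped values (sign reversed) divided by 10 − k. The outcome mean rises by r times that.
- k = 1: 1.539/9 = 0.171. With r = 0.3 the shift is 0.051 SD; with r = 0.5 it is 0.0855 SD.
- k = 2: (1.539 + 1.001)/8 = 0.3175. With r = 0.3 the shift is 0.095 SD; with r = 0.5 it is 0.159 SD.

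The same can be put without a correlation. If never-starters differ from the remaining SoroTouch participants by g SD, removing k of 10 shifts the arm mean by (k/10) × g. For k from 1 to 3 and g from 0.25 to 1.0, this runs from 0.1 × 0.25 = 0.025 SD to 0.3 × 1.0 = 0.30 SD.

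**Step 4: effect on false positives.** I simulated the step 3 model with 10 controls and a two-sided t-test at 0.05. At r = 0.5 the rejection rate is about 0.056 with one removed and 0.064 with two. At r = 0.3 it is about 0.052 and 0.055.

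**Step 5: check whether other text repairs the definition.** Section 10.6 says that all evaluated data should be used, but it does so while qualifying the rule on periods below 10 minutes a day. It does not return to the set anyone whom 10.1.1 has excluded. No all-randomised set or sensitivity analysis is stated.

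**The case against.** A reader might infer from 10.1.1 that the whole control arm is to be dropped, since every control receives no intervention. Taken word for word the sentence says this, but the rest of the protocol does not support it. Section 8.2.1 compares the two groups, 10.2 counts 20 analysed subjects, and 10.5.2 tests group differences by analysis of covariance. Controls are meant to be analysed, so the literal reading shows only that the sentence is badly worded.

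A reader might also put the power loss at 0.74, the figure for 8 vs 8. That needs two control losses as well, which this exclusion cannot cause. The matching case is 8 vs 10, at 0.791.

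The stronger objection is that few people may be affected. Participants consent to the programme, receive a loaned iPad (5.7) and 5,000 yen a month (15.1), have their learning time checked by staff (5.2.2) and are given encouragement (13.1.2). The exclusion covers only those with no use at all; partial use falls under the separate 10-minute rule. The bias figures rest on an assumed correlation and on never-starters being exactly the least engaged. They are small beside an assumed effect of 1.4 SD in a study declared exploratory. All of this stands, and it limits the size of the problem.

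It also stands that rewording 10.1.1 alone may not bring these people back. A never-starter discontinued under 6.4 before the month-1 CogEvo has no later assessment and drops out under any set that requires one.

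None of this makes the exclusion sound. It still acts on one arm only, and 8.2.1 still declares the intervention effective on statistical significance.

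**Conclusion.** The definition should be fixed. The no-intervention exclusion is undefined for the non-treatment arm and in practice works as a one-sided exclusion after randomisation. If never-starters tend to do worse, it favours SoroTouch.

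The size is modest and uncertain. For one or two never-starters the spurious shift is about 0.05 to 0.10 SD at a correlation of 0.3 and 0.09 to 0.16 SD at 0.5. Power is 0.819 or 0.791 against 0.841 with everyone kept. These figures depend on assumed counts and correlations, a two-sided test and the protocol's own effect size. They show scale and do not predict what will happen. With no never-starters the exclusion does no harm.

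**What to change.** Replace the sentence in 10.1.1 with: *All randomised subjects with at least one post-allocation assessment of the outcome, analysed in the arm to which they were allocated, whether or not they used SoroTouch.* This deletes the no-intervention exclusion and replaces 'post-intervention' with a term that applies to both arms.

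Reconcile this with 6.4, where item 8 and the end of observation at discontinuation may leave a never-starter with no post-allocation assessment. Unless the two sections are made consistent, the loss from the SoroTouch arm alone can continue by that route.

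The rewording of 10.1.1 is one sentence and adds no subjects or visits. Reconciling 6.4 is a further edit, whose cost depends on how the sponsor resolves it. The statistical price is slight dilution of the estimate by non-starters, who are part of the effect of offering the app. Because section 10 requires the protocol to be revised when the analysis plan changes, the edit should go through that route.
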